　　When incorrect or multiple registrations are found, the registration center should be notified at once.

● Usefulness Evaluation (Phase III)

1. Registration should take place, as a rule, within 14 days of obtaining consent.
2. The principal investigator or assistant investigators will obtain signed consent forms and confirm that participants satisfy the eligibility criteria, and that there is no conflict with the exclusion criteria. Registration forms should be filled in for participants who signed the consent form and sent it to the data center by fax or delivered it in person. The content of the registration forms will be verified at the data center to confirm eligibility. Necessary information for eligible cases will be entered into the system, and all cases will be randomly assigned to either the capnography group or the nasal pressure monitor group at a ratio of 1:1. At the data center, assignment results will be checked and sent to the principal investigator or assistant investigators by fax.
3. Patients who are registered once will not be removed from the database. When the same person is registered multiple times, the initial registration information (Registration No.) should always be used.

When incorrect or multiple registrations are found, the registration center should be notified at once.

* The principal investigator and assistant investigators must not commence the study until registration and assignment of all participants have been completed.

- - 1. **Assignment Adjustment Factors**

Assignment adjustment factors for the usefulness evaluation are procedure (EUS-FNA, ERCP, ESD and DBE), obesity (BMI ≥25, <25), and sex.

- - 1. **Registration Center Location**

Chiba University Hospital Date Center

Business hours: 09:00 – 17:00

Tel; [contact] ([name])

[contact]

- 1. **Handling of Ineligible Patients**

● Safety Evaluation (Phase II)

Patients who are not registered due to ineligibility or other reasons will be counted as non-registered participants and not included as study subjects. Such patients will receive an explanation from the principal investigator or assistant investigators regarding whether or not it is possible to register for the clinical study.

● Usefulness Evaluation (Phase III)

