In accordance with the Clinical Trials Act, in cases where the principal investigator determines that reporting to the Approved Clinical Study Review Board/Minister of Health, Labour and Welfare is required as described in “9.3. Reporting Diseases, etc. and Defects,” the principal investigator will prepare a Medical Device Diseases, etc., and Defect Report (Standard Form 9) and a Diseases, etc., Report (Medical Device) (Annex Form 2-2), and submit them to the Approved Clinical Study Review Board/Minister of Health, Labour and Welfare. Regular reports regarding diseases, etc., will be made to the Approved Clinical Study Review Board using the Regular Report Form (Standard Form 5).

1. Information Shared with Manufacturers/Retailers of Testing Equipment

When making 7-day or 15-day reports regard diseases, etc., such information will also be shared with manufacturers/retailers of testing equipment at the same time.

1. Handling Additional Information

When the principal investigator of the participating institution where the adverse event in question occurred acquires additional information regarding the adverse event, an additional report will be made to the head of the participating institution as promptly as possible. Procedures for handling additional information will be in accordance with 2) to 4) of this section.

1. Response based on the Pharmaceutical and Medical Device Safety Information Reporting System.

Post-marketing drugs will be handled based on the Pharmaceutical and Medical Device Safety Information Reporting System, and reports will be submitted to the Ministry of Health, Labour and Welfare as required.

- 1. **Regular Reports**

Regular reports will be submitted to the Approved Clinical Study Review Board and the Minister of Health, Labour and Welfare regarding diseases, etc., in accordance with the Clinical Trials Act. Regular reports will be submitted to the Approved Clinical Study Review Board as a rule each year after one year from the day on which the study plan was submitted to the Minister of Health, Labour and Welfare, within two months of the completion of such period. Reports to the Minister of Health, Labour and Welfare will be made within one month of the day on which the Approved Clinical Study Review Board expressed their opinion.

1. **Evaluation Items**
   1. **Primary Endpoint**

- Hypoxemia occurrence rate (SpO_2_ <90%): number of cases / total number of eligible participants

Basis for Primary Endpoint Selection

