The FAS will be all registered participants whose usefulness data is entered after randomization. However, those of them whose baseline data was not available and those who are seriously in bleach of the Study Protocol (no consent, registered outside the agreed period) will be excluded.

- - 1. **Per protocol set (PPS)**

PPS will be the population of FAS minus those cases that are seriously in bleach of the Study Protocol, in terms of research method or concurrent therapy.

1. Selection criteria violation
2. Exclusion criteria violation
3. Contraindicated drug violation
4. Contraindicated therapy violation
   - 1. **Safety analysis set (SAS)**

SAS will the registered patients who were fitted with the testing equipment (the monitor) at least once and underwent endoscopy under sedation.

- 1. **Target Number of Cases and Basis for Selection**

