**● Usefulness Evaluation (Phase III)**

The purpose of the usefulness evaluation is to prove that there is no difference in the incidence rate of hypoxemia (SpO2 <90%) between nasal pressure monitor group and capnography group, meaning that nasal pressure monitor is not inferior to capnography. According to reports, the incidence rate of declined SpO_2_ to under 90% in the endoscopic procedure under sedation is 12–47% when propofol is used as sedative,[4, 8, 9, 10] With regard to required number of registered patients, calculation based on 20% hypoxemia incidence rate, with non-inferiority margin of 15% for nasal pressure monitor against capnography, statistical power of 80% and significance level of 0.05 on both sides results in 224 patients for both groups (112 patients respectively).

- 1. **Handling Case Records**

In principle, the principal investigator and statistic specialists will decide on how the information on cases will be handled. In principle, the principal investigator and a statistic specialist will decide on how the information on cases will be handled.

- 1. **Handling Data**

When computing or analyzing data, as a rule, the data will be handled as shown below. If a question arises, it will be resolved through discussion between a statistic specialist and the study coordinator.

Missing data will not be supplemented. As sensitivity analysis, mixed-effects model for repeated measures, which compensates for data mission, will be used. Details will be contained in the Statistical Analysis Plan.

- 1. **Statistical Analysis Items and Plan**

● Safety Evaluation (Phase II)

Carry out analysis after the data is fixed following the completion of study involving all cases that are the subjects of safety evaluation. In the usefulness evaluation of all participants, the primary analysis will be the analysis of the FAS, and analysis of the PPS that complies with the Study Protocol will be carried out as a reference. Safety analysis will be carried out with the SAS.

Details of the statistical analysis will be determined in the Statistical Analysis Plan, which will be prepared elsewhere before the data is locked.

● Usefulness Evaluation (Phase III)

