Data from the usefulness evaluation will be analyzed after it is fixed following the completion of the study that involves all cases. In the usefulness evaluation of all participants, the primary analysis will be the analysis of the FAS, and analysis of the PPS that complies with the Study Protocol will be carried out as a reference. Safety analysis will be carried out with the SAS.

Details of the statistical analysis will be determined in the Statistical Analysis Plan, which will be prepared elsewhere before the data is locked.

- - 1. **Patient Background Analysis**

Patient data distribution and summary statistics will be obtained for each group by population. With regard to nominal variables, frequency of the category and proportion will be shown for each group. With regard to metric variables, summary statistics (number of cases, mean value, standard deviation, minimum value, median and maximum value) will be obtained for each group. In the comparison between two groups, Pearson's chi-square test will be used for nominal variables, but if the cells with expected frequency <5 account for 20% or more, Fisher’s exact test will be used. The t-test will be used for metric variables. Significance level will be 0.05 on both sides.

- - 1. **Usefulness Analysis**
       1. **Primary Analysis**

The main purpose of the study is to verify using the incidence rate of hypoxemia as primary endpoint that nasal pressure monitor is not inferior to capnography. Frequency and proportion in each group will be collated and **two-sided 95% confidence interval will be computed** When the upper limit of the 95% confidence interval in the comparison of hypoxemia incidence rate goes 15% lower than the non-inferiority margin, we deem that non-inferiority was proven.

To verify the null hypothesis that incidence rate of hypoxemia in both groups is the same in the primary analysis, Mantel–Haenszel test will be applied to the data stratified using assignment factors. Significance level will be 0.05 on both sides.

- - - 1. **Secondary Analysis**

Secondary analysis regarding usefulness will be carried out for the purpose of giving supplementary consideration to the results of primary analysis. No multiplicity adjustment will be carried out in the secondary endpoints analysis regarding usefulness .

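### The FAS drops randomised patients for unavailable baseline data, although the primary comparison needs no baseline value beyond the three assignment factors

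*Protocol*

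**What the plan says.** Protocol 11.1.1 starts from a broad set: "The FAS will be all registered participants whose usefulness data is entered after randomization". It then takes out two kinds of patient: "those of them whose baseline data was not available", and those in serious breach of the protocol (no consent, or registered outside the agreed period). This point concerns only the first.

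Protocol 11.5 makes this set decisive for Phase III: "the primary analysis will be the analysis of the FAS". The per protocol set is a reference analysis.

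The primary endpoint in 10.1 is "Hypoxemia occurrence rate (SpO_2_ <90%): number of cases / total number of eligible participants". Under 11.5.2.1, non-inferiority is judged from a two-sided 95% confidence interval against a 15% margin. In addition, a "Mantel–Haenszel test will be applied to the data stratified using assignment factors". Section 5.4.2 names those factors: "Assignment adjustment factors for the usefulness evaluation are procedure (EUS-FNA, ERCP, ESD and DBE), obesity (BMI ≥25, <25), and sex". Section 5.4.1 puts their entry before allocation: "Necessary information for eligible cases will be entered into the system", after which the patient is randomly assigned 1:1.

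**The concern.** The clause is a post-randomisation exclusion from the analysis that decides the trial. Such an exclusion can be defended when the analysis cannot be run without the missing value, for example a change from baseline. Here there is no such need. The outcome is a yes/no event during and after sedation, and the stratification variables exist for anyone who could be assigned. Any patient the clause removes is therefore one the primary analysis could have kept.

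The term is also open. Section 11.1.1 does not say which data count as baseline data. Section 7.1.1 lists nine groups of screening items, including neck circumference, sleep-apnea items, ECG and chest X-ray, none of which enters the primary analysis. Only patients are masked (Study Outline, Study Method). Investigators receive the allocation (5.6), and assistant investigators read the monitor records (7.1, note b). The protocol states no review of FAS exclusions masked to arm or outcome.

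At stake are some precision if the losses are unrelated to outcome, and the direction of the result if they are not.

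**Working it through.** **1. Does the primary analysis use any baseline value that could be missing?**

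| Element of the primary analysis | Baseline value needed | Known before assignment? |
|---|---|---|
| Proportion with SpO2 <90%, difference, 95% CI (10.1, 11.5.2.1) | None | Not applicable |
| Mantel–Haenszel test (11.5.2.1) | Procedure, BMI class, sex (5.4.2) | Yes (5.4.1) |

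Restricted to the three factors, the clause would remove essentially nobody. If it removes anyone, the reason must be an item that this analysis does not use.

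**2. The plan's own sample size.** Inputs from 11.2: 20% hypoxemia (taken for both arms), margin 15 percentage points, 80% power, two-sided 0.05.

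n per arm = (1.960 + 0.842)² × [0.2×0.8 + 0.2×0.8] / 0.15² = 7.849 × 0.32 / 0.0225 = 111.6, rounded up to 112, or 224 in total.

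This matches the stated figure exactly. The 224 therefore contains no allowance for exclusions; Phase II, by contrast, goes from 43 to 45 for drop-out.

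**3. Loss unrelated to outcome.** Power is computed by enumerating all pairs of binomial counts at 20% v 20%. A pass is a Wald 95% upper limit below 15%. The protocol gives no loss rate, so the losses are assumptions.

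| Patients per arm in FAS | Exact power |
|---|---|
| 112 (none lost) | 80.5% |
| 111 (one lost) | 79.8% |
| 110 (two lost) | 79.5% |
| 106 (about 5% lost) | 78.1% |

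The normal approximation gives the same picture: 80.1% at 112, 79.4% at 110, 77.9% at 106.

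**4. Worst-case sensitivity: one loss tied to outcome and arm.** Upper limit = (pT − pC) + 1.960 × √[pT(1−pT)/nT + pC(1−pC)/nC]. The counts are assumed and chosen close to the pass/fail boundary, with capnography at 22/112 = 0.1964.

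- Nasal pressure 27/112 = 0.2411: difference 0.0446, SE 0.0552, upper limit 0.0446 + 0.1081 = 15.3%. Fails.
- One hypoxemic nasal-pressure patient removed, 26/111 = 0.2342: difference 0.0378, SE 0.0550, upper limit 0.0378 + 0.1078 = 14.6%. Passes.
- For comparison, 26/112 with nobody removed gives 14.3%, which already passes.

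The reversal thus needs a result near the boundary and an exclusion in one particular direction.

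**The case against.** The strongest reply is that the clause will hardly ever operate. Screening is how patients are selected (7.1.1), and the data center verifies eligibility before assignment (5.4.1). Entry itself requires a room-air SpO2 and a systolic pressure (3.1), and an ECG or X-ray from up to 60 days before consent may be used (7.1). Baseline data should therefore exist before there is an arm or an outcome. This stands, and it is why the expected effect is small.

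A second reply is that the wording most naturally means a patient with no baseline record at all, with the operational meaning left to the statistical analysis plan. This stands in part. A reader might infer that one missing item, such as a neck circumference, is enough to exclude; the protocol does not say so. But even on the narrow reading, the exclusion serves no purpose in the primary analysis.

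A third concerns conduct. A reader might infer that availability is judged after the outcome is known, by staff who know the arm. No section says who judges it or when. The line in 11.3, that "the principal investigator and statistic specialists will decide on how the information on cases will be handled", is general and includes the statisticians. Original case report forms are held at the data center, in a system with access logs (15.1), and falsification counts as nonconformity (12). What remains is the absence of a stated safeguard, not evidence of misuse.

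A fourth is that false-pass calculations presuppose the bias they measure. With true rates of 20% v 35%, the chance of a false pass rises from 2.5% to 4.0%, 6.1% or 13.3% if hypoxemic nasal-pressure patients are dropped with probability 5%, 10% or 20%. This requires that nobody else is dropped. The last case means about 0.20 × 0.35 × 112 ≈ 8 such patients in one arm and none in the other. Any discretionary exclusion would show the same sensitivity. The objection is right, and these figures do not measure the effect of this clause.

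**Conclusion.** The point holds in a limited form. Section 11.1.1 contains an exclusion from the deciding set that the primary analysis does not need, rests on an undefined term, and has no stated masked review. If it never applies it is superfluous; if it applies, it removes a randomised patient whose outcome could have been counted.

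The likely size is small: about 0.6 to 1.0 percentage points of power for one or two patients lost per arm (80.5 − 79.8 = 0.7; 80.5 − 79.5 = 1.0, from rounded values), and 2.4 points at an assumed 5% loss (80.5 − 78.1). These figures assume 20% hypoxemia in both arms and losses unrelated to outcome. The reversal at 22/112 v 27/112 is a worst-case illustration of how little it takes near the boundary, not a forecast. The documents do not support a reading that selective removal is intended or expected.

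**What to change.** Delete the baseline-data exclusion from 11.1.1. Keep these patients in the FAS and stratify them by the assignment factors recorded at registration. In the 11.5.1 background tables, show missing baseline items as missing, and deal with them in the exploratory risk-factor analyses (10.3), where those items are actually used.

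The change belongs in the protocol, because 11.1.1 itself sets who enters the primary analysis; the statistical analysis plan should be worded to match. The cost is one clause and its counterpart, with no extra patients, visits or data.

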| After entering the treatment room for invasive endoscopy | For the Safety Evaluation (Phase II), patients will be fitted with both a capnography monitor and a nasal pressure monitor. After the nasal pressure monitor is fitted, do not turn on the capnography monitor, only check the display of the nasal pressure monitor, and administer sedatives. The capnography waveforms will be recorded and used later for waveform analysis along with those from the nasal pressure monitor.  Propofol and fentanyl will be used as sedatives, and will be administered by an endoscopist who has been fully trained in sedation by an anesthesiologist. The strength of the sedatives during the procedure will be controlled between BIS 60 and 80 as shown on the monitor in both groups. Prior to the administration of sedatives, oxygen will be administered through a transnasal catheter at a rate of 2 l/min. Local pharyngeal anesthesia (8% lidocaine spray) will be sufficiently administered until the vomiting reflex disappears. Propofol and fentanyl will be administered in accordance with a predetermined protocol (see below), while monitoring the patient’s sedation depth and suitably adjusting the dose of each drug. Administration will be stopped when the procedure has been completed, and if respiration rate drops to ≤8 bpm, naloxone will be administered. Patient response will be verified by calling out to the patient, and after checking that there are no cardiorespiratory dynamic problems, the patient will be allowed to leave the treatment room.  In cases where SpO_2_ is observed to have declined (<90), apnea lasts for ≥20 seconds, or a respiratory abnormality (≤8 bpm or abnormal waveform) accompanied by a decline in SpO_2_ (<95%) is observed during sedation, the doctor in change of sedation will report the respiratory abnormality to the endoscopy team, and measures will be taken to improve respiration (see 5.7). When such measures have been taken, details regarding the respiratory abnormality that caused them are recorded in the check sheet.  Monitoring data will be analyzed for up to three hours after the treatment in the Safety Evaluation (Phase II). Later, assistant investigators will analyze the monitor waveforms. |

● Usefulness Evaluation (Phase III)

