| Before entering the treatment room for invasive endoscopy | Patients who undergo invasive endoscopy will be assigned to either the nasal pressure monitor group or the capnography group and single-blinded by going through the following steps.   1. A signed consent form will be obtained from each participant, their eligibility verified, and participants registered. 2. Assignment results will be sent from the registration center to the principal investigator or assistant investigators. |
| --- | --- |
| After entering the treatment room for invasive endoscopy | In the Usefulness Evaluation (Phase III), both the capnography group and the nasal pressure monitor group will be sedated using one type of monitor, which will be the one used in the group to which they were assigned.  The method of sedation and response used in cases of respiratory abnormality are the same as those used in the Safety Evaluation (Phase II) (see 5.6).  In the usefulness evaluation, monitoring data will be analyzed for up to one hour after treatment. Later, assistant investigators will analyze the monitor waveforms. |

- 1. **Response to Respiratory Abnormalities**

In cases where SpO_2_ is observed to have declined (<90), apnea lasts for ≥20 seconds or a respiratory abnormality (≤8 bpm or abnormal waveform) accompanied by a decline in SpO_2_ (<95%) is observed during sedation, the doctor in change of sedation will report the respiratory abnormality to the endoscopy team, and measures will be taken to improve respiration (see 5.7).

When SpO_2_ drops to below 90%, oxygen will be increased, the patient will be stimulated (call their name), airway management will be carried out (head tilt, chin lift, or postural change), and propofol and fentanyl administration will be stopped or adjusted as required. In cases where such procedures do not improve the situation, a nasal airway tube will be inserted or the endoscope will be removed and artificial ventilation provided using an Ambu bag (a bag valve mask).

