When an adverse event is observed, the principal investigator or assistant investigators will immediately take appropriate measures, and if treatment is required they will inform the participant.

- 1. **Obtaining Information regarding Adverse Events**

With regard to all adverse events that occurred during the reporting period shown below, the principal investigator or assistant investigators will enter them in medical records and case report forms truthfully.

- 1. **Adverse Event Reporting Period**

All adverse events that occur between the first date on which the testing equipment is used and the day following the last day on which the testing equipment is used will be collected regardless of the causal relationship. Adverse events that are deemed to have a causal relationship with the testing equipment will be observed until such adverse events disappear or the symptoms stabilize.

All serious adverse events that occur before seven days after the last day on which the testing equipment is used will be reported, and such adverse events will be observed until they disappear or the symptoms stabilize. Adverse events that are deemed not to have any relationship with the testing equipment will be observed until they disappear or for 28 days after the completion (discontinuation) of the study.

The principal investigator or assistant investigators will enter all of the adverse events that occurred during the reporting period shown above in medical records and case report forms truthfully.

- 1. **Reporting Details Required for Evaluating Adverse Events**

1. Name of the adverse event.
2. Date on which the event occurred.
3. Date on which the outcome was decided.
4. Outcome: recovered (or disappeared), alleviated, recovered or disappeared with aftereffects, yet to recover, deceased, or unknown.
5. Procedure (use of testing equipment): as scheduled, discontinued, or not-applicable.
6. Other procedures: none, drug therapy, or other.
7. Severity: Not severe or severe.
8. Symptom evaluation: CTCAE (Ver. 4.0) Grade 1, 2, 3, 4 or 5.
9. Causal relationship with testing equipment: Yes, no.
10. Predictability: Known or unknown
    - 1. **Adverse Event Recoverability and Causal Relationship with Testing Equipment**

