(3) Impairment (the appearance of functional failure of such a degree that it hinders daily life).

(4) An event that may lead to impairment.

(5) An event that requires hospitalization or an extension of hospitalization in a hospital or clinic for treatment.

(6) A serious event similar to the cases described in (1) to (5).

(7) A congenital disease or abnormality.

Note: The “hospitalization’ mentioned in (5) does not include hospitalization or extension of hospitalization for retesting, follow-up testing or treatment, or hospitalization for the purpose of treatment or testing that was already scheduled to be performed during the timeframe of the study (scheduled surgery and testing). (However, events that newly occur during such hospitalization will be handled as an adverse event.)

- 1. **Serious Adverse Events Subject to Reporting**

All serious adverse events that occur during the study, and other serious adverse events that are suspected to have occurred due to testing equipment after the completion (discontinuation) of the study, will be reported.

Acute cardiorespiratory failure that occurs during the period in which adverse events are observed within the study period (from the commencement of sedation to the following day) will be defined as follows in accordance with CTCAE. Adverse events classed as Grade 3 or above will be reported as serious adverse events regardless of the causal relationship with the testing equipment.

| Grade 3 | Events that are not life-threatening, but which require general management using tracheal intubation or general anesthesia even after the measures described in “5.7. Response to Respiratory Abnormalities” as defined in the Protocol have been taken. |
| --- | --- |
| Grade 4 | Events that require resuscitation using cardiac massage and tracheal intubation due to deterioration in cardiovascular dynamics. |
| Grade 5 | Death. |

- 1. **Reporting Disease, etc., and Defects**

When the principal investigator comes to the knowledge regarding the disease/condition that are listed in the table below during the execution of the specific clinical study, they will report within the specified period.

**Table: Reporting Diseases, etc. (For Specific Clinical Study involving Medical Devices that are Unapproved or Not Listed for Use under National Health Insurance)**

|  |  |  | Report to the Pharmaceuticals and Medical Devices Agency (PMDA) | Report to Clinical Study Review Board |
| --- | --- | --- | --- | --- |

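### The safety analysis set requires that endoscopy took place, so a patient sedated on the monitor whose endoscopy is cancelled before scope insertion because of a sedation event is left out of the adverse event rate

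*Protocol*

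**What the plan says.** Protocol section 11.1.3 defines the safety analysis set as the registered patients who were "fitted with the testing equipment (the monitor) at least once and underwent endoscopy under sedation". The two conditions, monitor fitted and endoscopy undergone, are joined by an "and". Section 11.5 uses this set in both phases: "Safety analysis will be carried out with the SAS". The statistic is the frequency of adverse events, with an exact binomial 95% confidence interval for each group (section 11.5.3).

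Other sections fix when exposure and event collection begin:

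- Section 5.6: once the nasal pressure monitor is on, the operator is to "only check the display of the nasal pressure monitor, and administer sedatives". Phase III uses the same method of sedation with the assigned monitor.
- Section 8.5 sets the collection window: "All adverse events that occur between the first date on which the testing equipment is used and the day following the last day" of use.
- Section 9.2 counts acute cardiorespiratory failure "from the commencement of sedation to the following day", and Grade 3 or above is a serious adverse event whatever its cause.

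Section 5.7 describes one response to a desaturation that does not resolve: "the endoscope will be removed and artificial ventilation provided using an Ambu bag".

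**The concern.** A safety set should contain everyone exposed. Here membership also depends on a later step, and a safety event can prevent that step. The interval at issue runs from the first sedative dose to insertion of the endoscope. The protocol treats the start of sedation as a period to watch closely: section 7.1.2.1 asks for most vital signs every 2.5 minutes during the first 15 minutes. Section 8.7.2 lists hypotension, anaphylactoid symptoms, bronchospasm and transient apnea among the expected effects of propofol, and nothing ties these to insertion.

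If such an event leads the team to cancel the endoscopy, the patient fails the second condition because of the outcome that the set is meant to measure. Phase II is where this matters most: it is the safety evaluation, and its results go to the IDMC before Phase III opens. The full analysis set does not clearly recover such a patient there, because section 11.1.1 defines it by data entered after randomization and Phase II has no assignment.

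**Working it through.** No figure in the protocol rests on this definition, so there is none to reproduce. The check compares the rules and then illustrates the size.

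**Step 1. Follow a patient through the rules.**

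| Situation | Collected under 8.5 or 9.2? | In the safety set under 11.1.3? |
| --- | --- | --- |
| Monitor fitted, sedated, endoscopy completed | Yes | Yes |
| Monitor fitted, sedated, endoscope inserted, then removed for a respiratory event (5.7) | Yes | Yes: endoscopy was undergone, though not completed |
| Monitor fitted, sedated, endoscopy cancelled before insertion because of a sedation event | Yes | No: the second condition fails |

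Only the third row is a gap. The event is collected, but the patient is in neither numerator nor denominator.

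**Step 2. Size within one cohort or group.** Inputs: Phase II target 45 and Phase III target 112 per group (section 11.2). Assumption: k patients have an event of a given type, all k are cancelled before insertion, and nobody else has that event. The protocol gives no value for k. With all N patients kept, the rate is k/N. Under the definition as written it is 0/(N − k).

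The exact (Clopper-Pearson) 95% upper limit for x events in n patients is the 0.975 quantile of Beta(x + 1, n − x). For x = 0 it reduces to 1 − 0.025^(1/n); for example, 1 − 0.025^(1/44) = 8.0%.

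| N | k | All kept: rate (upper limit) | As written: rate (upper limit) |
| --- | --- | --- | --- |
| 45 | 1 | 1/45 = 2.2% (11.8%) | 0/44 = 0% (8.0%) |
| 45 | 2 | 2/45 = 4.4% (15.1%) | 0/43 = 0% (8.2%) |
| 45 | 3 | 3/45 = 6.7% (18.3%) | 0/42 = 0% (8.4%) |
| 112 | 1 | 1/112 = 0.9% (4.9%) | 0/111 = 0% (3.3%) |
| 112 | 3 | 3/112 = 2.7% (7.6%) | 0/109 = 0% (3.3%) |

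**Step 3. The same loss in an overall rate.** If 10 of 45 patients had some adverse event (an assumed count) and one of them were dropped, the rate would move from 10/45 = 22.2% to 9/44 = 20.5%. The effect is marked for a single rare event type and small for all adverse events together.

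**Step 4. Direction between groups.** Suppose each Phase III group has one such event, 1/112 in each, so the true difference is 0. If only the nasal pressure patient is dropped, nasal pressure minus capnography becomes 0 − 0.9 = −0.9 percentage points. If only the capnography patient is dropped, it becomes +0.9. The sign depends on which group loses the patient.

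**The case against.** The strongest reply is that the gap is narrow and little is lost.

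- **The set requires endoscopy undergone, not completed.** This stands. A reader might infer that any procedure abandoned for a sedation event leaves the set. The text does not support that: the abandonment in section 5.7 is removal of an endoscope already in place, and that patient remains. Because the qualifying term is not defined, a clarification would help there too.
- **Nothing shows that the gravest cases are the ones removed.** This stands. Sedation lasts through the whole procedure, monitoring continues for hours in Phase II and one hour in Phase III, and the protocol does not say when the worst events occur.
- **The bias need not favour either monitor in the comparison.** This stands, as Step 4 shows. Even within a group, an event-free patient whose endoscopy is cancelled for another reason also leaves the denominator, which slightly raises the rate (1/45 = 2.2% becomes 1/44 = 2.3%). Only event-caused cancellation has a fixed direction.
- **The event is not lost.** This stands. It is collected, and reported if serious. The principal investigator may refer serious events to the IDMC (section 11.6), and section 11.5.4 does not confine the IDMC's results to the safety set. In Phase III, hypoxemia is analysed in the full analysis set, which requires usefulness data rather than endoscopy, so a desaturation at induction can still count there.
- **The analysis plan can settle the wording.** This stands in part. Section 11 lets the plan revise the overview, but the protocol does not leave the definition open: it states a rule that excludes these patients.

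**Conclusion.** The definition should be changed. As written, it excludes a patient who was fitted with the monitor, sedated, and then had the endoscopy cancelled before insertion because of a sedation event, although sections 8.5 and 9.2 count that patient's event. Exclusion of this kind lowers the adverse event rate of the Phase II cohort or Phase III group in which it occurs. It does not imply a bias towards either monitor, and the primary hypoxemia analysis does not rest on this set.

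The cases are probably rare, and the protocol gives no frequency. One assumed case in Phase II, the only one of its event type, changes 2.2% (upper limit 11.8%) to 0% (upper limit 8.0%). In one Phase III group it changes 0.9% (upper limit 4.9%) to 0% (upper limit 3.3%). If other patients have events of the same type, the change is smaller. The case for acting is that the loss depends on the outcome, falls in the set meant to describe safety, and costs almost nothing to avoid.

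**What to change.** Reword section 11.1.3 so that the safety analysis set is all registered patients who were fitted with a study monitor and received any study sedative (propofol or fentanyl), whether or not endoscopy was begun or completed. Carry the same sentence into the statistical analysis plan. If the team also wants rates among patients in whom endoscopy began, these can be shown as a supplementary table.

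The cost is one sentence. The adverse events, sedation times and sedative doses are already recorded under sections 7 and 8. Sample size, primary analysis and patient management do not change.
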